#### 10.5.2 Assessment of expectedness of an SAE by the CI

The CI or delegate will assess all SARs for expectedness with reference to the criteria in Table 7.

If the event is unexpected, it will be classified as a Suspected Unexpected Serious Adverse Reaction (SUSAR).

The CI will review all SAEs submitted and may request further information from the site research team for any given event to assist in this review.

**Table 7:** Definition of Expectedness

| Category          | Definition                                                                                                                                                                                                                                                         |
|-------------------|--------------------------------------------------------------------------------------------------------------------------------------------------------------------------------------------------------------------------------------------------------------------|
| Expected   | An adverse event that is consistent with known information about the trial related procedures or that is clearly defined in the reference safety information:

Summary of product characteristics (SmPC) for oral prednisolone

SmPC for dexamethasone |
| Unexpected | An adverse event that is not consistent with known information about the trial related procedures or that is not clearly defined in the reference safety information.                                                                                |

### 10.5.3 Provision of follow-up information

Following reporting of an SAE for a participant, the participant should be followed up until resolution or stabilisation of the event. Follow-up information should be provided to BCTU via the trial database. The site should also email the trial mailbox to inform BCTU that follow up information has been submitted.

## 10.6 Reporting SAEs to Third Parties

### 10.6.1 Data Monitoring Committee (DMC)

The independent DMC may review any SAEs at their meetings.

### 10.6.2 MHRA, REC and RGT

BCTU will report details of all SARs (including SUSARs) to the Medicines and Healthcare Products Regulatory Agency (MHRA), Research Ethics Committee (REC) and UoB Research Governance Team (RGT) annually from the date of the Clinical Trial Authorisation, in the form of a Development Safety Update Report (DSUR).

In addition, BCTU will report a minimal data set of all individual events categorised as a fatal or life threatening SUSAR to the MHRA, REC and RGT within 7 days of being notified. Follow-up information will be provided within an additional 8 days.

All other events categorised as non-life threatening/non-fatal SUSARs will be reported within 15 days of being notified.

The MHRA, REC and RGT will be notified immediately if a significant safety issue is identified during the course of the trial.

Details of all SUSARs and any other safety issues which arise during the course of the trial will be reported to PIs. A copy of any such correspondence should be filed in the ISF and Trial Master File (TMF).

---

## 10.7 Urgent Safety Measures

The Clinical Trials Regulations make provision for the Sponsor and PIs to take appropriate Urgent Safety Measures to protect a research participant from an immediate hazard to their health and safety. This measure can be taken before seeking approval from MHRA and REC.

If any urgent safety measures are taken, BCTU shall immediately and in any event no later than 3 days from the date the measures are taken, give written notice to the MHRA and REC of the measures taken and the reason why they have been taken.

## 10.8 Follow-up of Pregnancy Outcomes

The trial population may include women of child bearing potential. Considering the level of risk and the factors outlined below, no additional monitoring of pregnancy or pregnancy outcomes is planned, other than would occur as part of routine clinical practice for the condition and treatments used.

- The trial treatments are well-established and will be used in accordance with their existing licences and routine clinical practice
- The treatment period is relatively brief
- Use of the trial treatments is not contraindicated in pregnancy
- The trial is unlikely to add to the known safety profile of the treatments under study in pregnancy
- Standard routes for reporting of suspected side effects (including the yellow card scheme) will be available to investigators, as in routine clinical practice

## 11 DATA HANDLING AND RECORD KEEPING

### 11.1 Source Data

Source data is defined as all information in original records and certified copies of original records of clinical findings, observations, or other activities in a clinical trial necessary for the reconstruction and evaluation of the trial. In order to allow for the accurate reconstruction of the trial and clinical management of the participants, source data will be accessible and maintained.

Some data variables may be entered directly onto the CRF, these are clearly identified and detailed in Table 8.

**Table 8:** Source Data

| Data                          | Source                                                                                                                                                                                          |
|-------------------------------|-------------------------------------------------------------------------------------------------------------------------------------------------------------------------------------------------|
| Audiometry Outcomes           | The clinical notes provide the source data, transcribed at site onto the participant CRFs                                                                                                       |
| Participant Reported Outcomes | The original participant-completed paper form is the source and will be forwarded directly to BCTU                                                                                              |
| Clinical event data           | The original clinical annotation is the source document. This may be found on clinical correspondence, or electronic or paper participant records. Clinical events reported by the participant, |

|                        |                                                                                                                                        |
|------------------------|----------------------------------------------------------------------------------------------------------------------------------------|
|                        | either in or out of the clinic (e.g. phone calls), must be documented in the source documents.                                         |
| Health economics data  | Data will be completed directly on to the CRF via interview with the participant and this will constitute the source data.             |
| Home hearing test data | Source data will be HearX server                                                                                                       |
| Recruitment            | The original record of the randomisation is the source. It is held on BCTU servers as part of the randomisation and data entry system. |
| Withdrawal             | Where a participant expresses a wish to change their level of participation, the conversation must be recorded in the medical record.  |

## 11.2 Case Report Form Completion

CRFs should be completed for each individual participant.

The CRFs will include, but not be limited to, the forms listed in Table 9.

**Table 9:** List of trial specific CRFs

| Form Name                    | Schedule for submission                                                                                                                                                      |
|------------------------------|------------------------------------------------------------------------------------------------------------------------------------------------------------------------------|
| Screening log                | When a patient presents with ISSNHL and is considered for approach to participate in the STARFISH trial                                                                      |
| Contact details form         | Following consent                                                                                                                                                            |
| Randomisation CRF            | At the point of randomisation                                                                                                                                                |
| Clinic visit form            | At baseline (i.e. following consent and randomisation);
At 2nd injection visit (if applicable);
At 3rd injection visit (if applicable);
At 6 weeks;
At 12 weeks. |
| Participant-complete booklet | At baseline (i.e. following consent and randomisation);
At 6 weeks;
At 12 weeks.                                                                                       |

|                                  |                                                                        |
|----------------------------------|------------------------------------------------------------------------|
| Serious Adverse Event Form       | In accordance with section 10                                          |
| Trial Exit/Change of status Form | At the point of becoming aware of withdrawal/change of status or death |

Data should be submitted according to section 11.5 in a timely manner i.e. within four weeks of submission schedule. If data has not been provided within four weeks of the submission schedule detailed in the above table then a reminder email will be sent to sites. If data is consistently not provided in this timeframe BCTU will directly contact the site to ascertain the reason for the delay. This may also be escalated to the site's senior management and can trigger a monitoring visit.

In all cases, it remains the responsibility of the PI to ensure that the CRFs has been completed correctly and that the data are accurate. This will be evidenced by the signature of the PI or delegate(s). The Site Signature & Delegation Log will identify all those personnel with responsibilities for data collection. The delegated staff completing the CRF should ensure the accuracy, completeness and timeliness of the data reported. This will be evidenced by signing and dating the CRF.

Data reported on CRFs will be consistent with the source data and any discrepancies will be explained. All missing and ambiguous data will be queried via a Data Clarification Form (DCF). Staff delegated to complete CRFs will be trained to adhere to trial specific working instructions on CRF Completion.

The following guidance applies to data:

- Rounding conventions - rounding should be to the nearest whole number: If the number you are rounding is followed by 5, 6, 7, 8, or 9, round the number up. (e.g. 3.8 rounded to the nearest whole number is 4). If the number you are rounding is followed by 1, 2, 3 or 4, round the number down. (e.g. 3.4 rounded to the nearest whole number is 3).
- Trial-specific interpretation of data fields – where guidance is needed additional information will be supplied.
- Entry requirements for concomitant medications (generic or brand names) – generic names should be used where possible.
- Repeat tests – the data used to inform clinical decisions should always be supplied. If a test is repeated, it is either to confirm or clarify a previous reading. Confirmatory tests should use the original test values.
- Protocol and GCP non-compliances should be reported to BCTU on awareness.

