#### **5.1 Consent Procedure**

Participants with confirmed ISSNHL will be approached about the trial by their clinical care team during the standard clinical appointment following referral to secondary care.

A Participant Information Sheet (PIS) will be provided to facilitate this process, which may be presented electronically. Participants will also be invited to watch a short explanatory video on their own smartphone, tablet or hospital computer at <https://entintegrate.co.uk/starfish>. The PI or delegate will ensure that they adequately explain the aim of the trial, trial interventions, and the anticipated benefits and potential hazards of taking part in the trial to the participant. They will also explain that participation is voluntary and that the participant is free to decide to take part and may withdraw from the trial at any time without affecting their care.

---

The participant will be given sufficient time to read the PIS and discuss their participation with others outside of the clinical or research team. The participant will be given the opportunity to ask questions before electronically signing and dating the latest version of the Informed Consent Form (ICF). Paper copies of the PIS and ICF will also be available from the Trial Office and will be printed or photocopied onto the headed paper of the local NHS Trust.

**Given the urgent need to commence treatment for the condition, randomisation and commencement of treatment should ideally occur on the same or next working day after written consent has been gained.**

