### 6.5 Blinding

Participant blinding is not required given the method of primary outcome assessment, which is objective from the perspective of the participant. PPI during study development also suggested that knowledge of treatment allocation is unlikely to (directly) influence the primary outcome. It is also not practical given the different routes of drug administration between the arms of the trial.

The audiologist assessing the primary outcome (the pure tone audiogram) will be blinded to the randomised treatment allocation (18) as the outcome can be considered subjective from the perspective of the assessor. The ENT team member reviewing the participant routinely at that time will examine the ear prior to audiological testing and confirm to the audiologist that

---

the ear is appropriate for testing, without disclosing the treatment allocation. Findings that may make the ear non-appropriate may be earwax or an infection. Wax will be removed to allow testing to proceed, and an infection will be treated and testing arranged at the nearest opportunity. If there needs to be a delay in testing, this will be recorded with the reason. The audiologist therefore will not need to look in the participant's ear.

In addition, where feasible, the pre-injection PTA tests should be conducted by an audiologist not recording later outcomes for the trial. The audiologist(s) performing the pre-injection audiogram and outcome testing will be recorded allowing assessment for outcome bias. In the small proportion where the same audiologist performs both tasks and would therefore be unblinded to the pre-treatment hearing thresholds.

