- Co-phenylcaine or xylocaine spray – 4-6 sprays are administered directly into the ear canal with the study participant's head turned away to allow the liquid to remain in contact with the eardrum. The anaesthetic may take up to 10 minutes to be effective.

**Intratympanic injection:** Any local anaesthetic is removed using microsuction. Under visual guidance, the spinal needle should be passed through the tympanic membrane, ideally in the antero-superior quadrant in order to avoid the round window and ossicular chain. Dexamethasone is slowly injected, looking for the fluid level as it passes up the tympanic membrane. Once the middle ear is filled to the level of the needle, the needle can be withdrawn. Rapid filling of the middle ear should be avoided to reduce the risk of discomfort. The approximate volume of steroid injected into the middle ear should be recorded.

**Positioning the participant after injection:** Following the injection, the study participant should keep their head turned away from the injected ear and remain lying down in that position for 30 minutes to maximise uptake of steroid through the round window.

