## 9 TRIAL PROCEDURES

### Baseline

The following should be performed and/or collected:

- Informed consent
- Medical history
- Concomitant medication check
- Demographic information
- Pure tone audiogram (0.5-8.0kHz range) - should be performed within 3 days prior to commencement of treatment
- AB phoneme speech testing- recommended to be performed on same day as pure tone audiogram or if not practicable within next working day
- Participant completed questionnaires to include SSQ, VRBQ, TFI, HUI3, ICECAP-A
- Oral steroid arm and combination treatment arm- prescribe oral steroids

- 
- Intratympanic injection arm and combination treatment arm - 1st intratympanic injection (for the combination arm, injection should be given within a period  $\pm 4$  days of starting oral steroids).

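### Baseline questionnaires are set after randomisation in unblinded participants, and the baseline speech test is not tied to the start of treatment, so these secondary-outcome baselines can be affected by allocation

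*Protocol*

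**What the plan says.** **Booklet.** In the protocol, section 11.2, Table 9, the entry for the participant-complete booklet begins "At baseline (i.e. following consent and randomisation". The baseline clinic visit form has the same entry. Section 9 gives the booklet's contents: "Participant completed questionnaires to include SSQ, VRBQ, TFI, HUI3, ICECAP-A". Section 9 and Table 3 put randomisation or first treatment under the same Baseline heading as the questionnaires, and neither says that the questionnaires come first.

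**Blinding.** Section 6.5 says "Participant blinding is not required given the method of primary outcome assessment". That argument concerns the audiogram only.

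**AB speech test.** Section 9 says "AB phoneme speech testing- recommended to be performed on same day as pure tone audiogram or if not practicable within next working day". The audiogram must fall in the three days before treatment starts; the AB test carries no such condition. Section 5.1 adds that "randomisation and commencement of treatment should ideally occur on the same or next working day after written consent has been gained", and section 9 lists "Intratympanic injection arm and combination treatment arm - 1st intratympanic injection" within the same Baseline visit.

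**Use in the analysis.** Section 14.2 adjusts outcomes for baseline values where they exist. Section 14.2.1 puts the baseline score in the model, and section 14.2.2 applies that model to all continuous secondary outcomes. Section 15.1 uses utility data from baseline and 12 weeks.

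**The concern.** A baseline covariate is safe to adjust for because allocation cannot have influenced it. A self-rated score given by someone who has just learned their arm lacks that protection, and randomisation does not restore it. If knowledge of allocation moves the baseline differently between arms, adjustment carries part of that movement into the estimated treatment difference.

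The AB test raises a related problem. If it is done after the first injection, the ear under test has just had dexamethasone instilled (section 7.3: "Once the middle ear is filled to the level of the needle, the needle can be withdrawn"). The oral-only arm has no counterpart to this, although its first dose may also come before the test.

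At stake are the SSQ, which section 14.1 presents as a key secondary outcome with adequate power, the VRBQ, TFI and AB score, and the starting values for HUI3 and ICECAP-A.

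**Working it through.** **1. Is the order really fixed after randomisation?** Table 9 has separate entries for forms due after consent (contact details) and at randomisation (randomisation CRF). The booklet's entry places baseline after both. Its other entries, 6 and 12 weeks, are assessment times, and the text below the table gives a separate four-week allowance for sending data in. No other section puts the questionnaires before randomisation.

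**2. Can the AB test follow treatment?** Its window runs from the audiogram day to the next working day and is only recommended. The audiogram may be on the day treatment starts, and treatment should ideally start on the day of consent or the next working day. These windows overlap, so an AB test after the first dose or injection is permitted. It is not scheduled.

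**3. Which baselines are unaffected?** The audiogram is needed for eligibility (section 4.1) and for minimisation (section 6.4.3), so it precedes randomisation. The other minimisation variables are also entered before allocation.

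**4. The plan's own SSQ power.** Inputs from section 14.1: 157 per arm, difference 0.65, SD 1.9, alpha 0.025 (two-sided, from section 14.2).
- Standard error = 1.9 × √(2/157) = 0.214
- 0.65 / 0.214 = 3.03; 3.03 − 2.24 = 0.79; power = 78.5%

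This agrees with the stated power of just under 80%. The point disputes no sample size or power figure.

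**5. Size of a covariate-induced shift in SSQ.** Let *s* be the between-arm shift in baseline score caused by knowing the allocation, and *b* the slope of the 12-week score on baseline. With no other effect, the adjusted difference moves by −*b* × *s*. **Neither *s* nor *b* is in the documents; both are assumptions.** The error column is the two-sided rate at a true null against a nominal 0.025. It takes the baseline-to-outcome correlation equal to *b*, so the residual SD is 1.9 × √(1 − *b*²).

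| *b* | *s* | Shift, *b* × *s* (absolute) | % of 0.65 | Error rate |
|---|---|---|---|---|
| 0.3 | 0.1 | 0.03 | 4.6 | 0.027 |
| 0.3 | 0.2 | 0.06 | 9.2 | 0.031 |
| 0.3 | 0.3 | 0.09 | 13.8 | 0.039 |
| 0.5 | 0.1 | 0.05 | 7.7 | 0.030 |
| 0.5 | 0.2 | 0.10 | 15.4 | 0.047 |
| 0.5 | 0.3 | 0.15 | 23.1 | 0.077 |
| 0.7 | 0.1 | 0.07 | 10.8 | 0.041 |
| 0.7 | 0.2 | 0.14 | 21.5 | 0.093 |
| 0.7 | 0.3 | 0.21 | 32.3 | 0.192 |

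This treats baseline as a covariate for a single follow-up comparison. Section 14.2.1 also lists baseline among the modelled assessment times, and that is not represented here.

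**6. Net direction.** The 12-week SSQ is also self-rated by unblinded participants. If reporting shifts by the same *s* at both times, a clean baseline leaves a bias of *s*, while a shifted baseline leaves *s*(1 − *b*). With *s* = 0.2 and *b* = 0.5 that is 0.20 against 0.10. The table is therefore the covariate's contribution and not the total bias.

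**The case against.** **Table 9 is a schedule for submitting forms.** On this view the bracket says when a form is filed and not when the data arise. It applies equally to the clinic visit form, whose audiogram must predate randomisation, and section 9 lists the questionnaires ahead of treatment. For the clinic form this stands: it is largely transcription, and entering it after allocation does no harm. For the booklet it fails. The entries are assessment times, submission has its own allowance, and the order of the list in section 9 is not stated to be binding and does not place the questionnaires relative to randomisation.

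**The AB sequence needs several things to coincide.** The audiogram must fall close to the injection, same-day AB testing must be impracticable, and the injection must come first. This stands. A reader might infer that AB testing after injection is built into the schedule and depresses the baseline, so that the injection arms appear to recover more speech. The documents do not support that. Section 8.3.2 seeks a maximum recognition score by raising the presentation level in steps, so attenuation from middle-ear fluid mainly changes the level at which the maximum is reached. The exceptions are where audiometer output or discomfort sets the limit. Nor does the recovery classification in Table 2 need the baseline AB score.

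**The SSQ figures are assumed and their direction is open.** This stands, as step 6 of the working shows.

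**Conclusion.** The point holds for a defined set of measures. Followed as written, the protocol collects the baseline SSQ, VRBQ, TFI, HUI3 and ICECAP-A from participants who already know their arm, and it leaves the baseline AB test free to follow first treatment. It then uses these values as covariates or economic starting values.

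A reader might infer that the trial's adjustment covariates in general are not true baselines. That is not so: the primary outcome's audiogram baseline and the minimisation variables are measured before randomisation, and the primary analysis is untouched by this point. A reader might also infer a known SSQ bias in a known direction. The documents support neither. The range of 0.03 to 0.21 points (5% to 32% of the MCID) rests wholly on assumed shifts and slopes, and its net effect depends on whether reporting also shifts at follow-up. The AB effect is probably small.

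This is an avoidable weakness in secondary and economic outcomes. It should be corrected because the correction is cheap.

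**What to change.** Amend Table 9, section 9 and Table 3 to agree that the questionnaires and the baseline AB test are completed after consent and before randomisation or, failing that, before allocation is disclosed and before first treatment. Add a completion check to the randomisation form; section 6.4.2 already requires every item on that form to be answered before a participant can be randomised.

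Record the time of any late baseline measure relative to randomisation and to first treatment. Keep such values in the main analysis, and run a sensitivity analysis that does not use baselines taken after allocation or treatment. Setting late AB values to missing in the main analysis is not advised, because lateness could differ by arm and would then create arm-dependent missing covariates.

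The cost is a few minutes of questionnaires moved ahead of allocation and edits to two tables, one section and one form. The change concerns the order of measurement only and alters no dose, treatment schedule, sample size or power figure.
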